## Abstract

**Background:**

Total knee arthroplasty (TKA) is currently the main treatment for end-stage knee disease. The number of cases of TKA in China increased from 53,880 in 2011 to 374,833 in 2019, representing a 5.9-fold increase. Moderate to severe pain often occurs after TKA, which seriously affects postoperative rehabilitation, patient satisfaction, and overall outcome. Multimodal analgesia is considered the ideal solution. Adequate postoperative analgesia can not only reduce pain, opioid consumption, and, consequently, opioid-related adverse events, but can also reduce the length of hospital stay and costs and improve rehabilitation and patient satisfaction.

**Objective:**

Effective multimodal pain management in the early postoperative period is essential for anesthesiologists. Additional studies have demonstrated that a low-dose intravenous infusion of ketamine can be administered as an adjuvant drug to alleviate acute postoperative pain. Therefore, we aim to appraise the efficacy and safety of intraoperative intravenous injection of S(+)-ketamine to relieve acute pain after TKA in older patients.

**Methods:**

This is a protocol for a randomized, placebo-controlled trial. A total of 144 participants aged 65 years and older undergoing TKA will be randomly allocated into the S(+)-ketamine and placebo groups in a 1:1 ratio. S(+)-ketamine or the placebo will be intravenously administered at 0.3 mg/kg/h during the operation by anesthesiologists. Blinded evaluation by trained investigators will be completed at 2 hours, 24 hours, and 48 hours after surgery. The primary outcome measure will be the numeric rating scale score at rest and movement at 24 hours after surgery. The secondary outcomes will include the numeric rating scale scores at rest and movement at 2 hours and 48 hours after surgery, the number of patients who require additional analgesics during the first 48 hours after operation, the total consumption of opioids or nonsteroid anti-inflammatory drugs during the first 48 hours after operation, and adverse events at 2, 24, and 48 hours after operation.

**Results:**

The protocol was registered at Clinical Trials.gov on February 26, 2022. It was performed in accordance with the approved guidelines and regulations of the participating institutions. Recruitment began in April 2022. Data collection is expected to conclude in September 2024. Study completion is expected in December 2024.

**Conclusions:**

A randomized, controlled, clinical study was designed to observe the analgesic effect of intraoperative intravenous administration of a lower dose of S(+)-ketamine (0.3 mg/kg/h) in older patients after TKA surgery. The protocol will appraise the efficacy and safety of intraoperative intravenous injection of S(+)-ketamine to relieve acute pain after TKA in older patients who may benefit from the administration of S(+)-ketamine.

**Trial Registration:**

ClinicalTrials.gov NCT05289050; https://clinicaltrials.gov/ct2/show/NCT05289050

**International Registered Report Identifier (IRRID):**

DERR1-10.2196/53063

## Introduction

Total knee arthroplasty (TKA) is currently the main treatment for end-stage knee disease. The number of cases of TKA in China increased from 53,880 in 2011 to 374,833 in 2019, representing a 5.9-fold increase [1]. Moderate to severe pain often occurs after TKA [2], which seriously affects postoperative rehabilitation, patient satisfaction, and overall outcomes [3,4]. Multimodal analgesia is considered the ideal solution. Adequate postoperative analgesia can not only reduce pain, opioid consumption, and, consequently, opioid-related adverse events, but can also reduce the length of hospital stay and costs and improve rehabilitation and patient satisfaction [5].

Opioids are effective for acute postoperative pain, but they have numerous adverse effects (eg, respiratory depression and nausea), especially in older patients. In addition, the use of excessive opioids may pose a risk of opioid addiction [6]. Despite encouraging results and rapid recovery after the use of perioperative local infiltration analgesia and nerve block agents, pain management can be further optimized [7]. Therefore, effective multimodal pain management in the early postoperative period is essential for anesthesiologists.

Ketamine has been widely used in anesthesia to relieve postoperative pain. It mainly acts on the N-methyl-D-aspartate (NMDA) receptor to produce sedative, analgesic, and anesthetic effects [8,9]. S(+)-ketamine is an effective S-enantiomer of racemic ketamine with a greater affinity than ketamine (approximately 2- to 4-fold) for NMDA receptors, thereby producing stronger sedative and analgesic effects and fewer adverse events, and it has been used to prevent central sensitization [10-13]. Opioids, such as remifentanil, may lead to hyperalgesia and more analgesic requirements. A clinical study showed that IV ketamine improved the analgesic effect of fentanyl and lessened hyperalgesia [14].

Aggressive management of TKA pain has multiple benefits, such as shortening the length of hospital stay, preventing postoperative complications, and accelerating patient recovery [15]. Therefore, S(+)-ketamine requires further investigation, and the following questions must be addressed: What is the ideal dosage of S(+)-ketamine infusion for the prevention of postoperative acute pain? Can older patients experience a beneficial effect after surgery? To answer these questions, a randomized, controlled, clinical study was designed to observe the analgesic effect of intraoperative intravenous administration of a lower dose of S(+)-ketamine (0.3 mg/kg/h) in older patients after TKA surgery.

## Methods

### Objective and Trial Design

This clinical study was designed to observe the analgesic effect of a lower intravenous dose of S(+)-ketamine (0.3 mg/kg/h) in patients after TKA surgery.

This is a single-center, randomized, single-blind, controlled, clinical trial in older patients undergoing TKA under general anesthesia. Eligible patients will be randomized to receive S(+)-ketamine (n=72) or a placebo equivalent, 0.9% sodium chloride (n=72), in a ratio of 1:1. Patients will be randomized using a computer-generated list. The anesthetist nurse and the pharmacist will not be blinded and will not partake in the following research, but the follow-up evaluators will be blinded in the trial.

### Recruitment and Study Setting

A researcher with a detailed understanding of the study protocol (ie, study objective, inclusion and exclusion criteria, and benefits and risks for patients) will present the protocol to the patients and answer any questions in a concise and comprehensive manner. All patients are required to provide written consent before surgery (Figure 1).

**Figure 1 figure1:**
[figure not shown]
Consolidated standards of reporting trials flow diagram describing patient progress throughout the study. TKA: total knee arthroplasty.

### Inclusion Criteria

The inclusion criteria include patients who have an American Society of Anesthesiologists physical status of I-III; understand the study in detail and voluntarily sign the informed consent form; are to be treated with TKA surgery under general anesthesia; are 65 years or older, regardless of sex; can communicate normally; have no contraindications to drugs, such as midazolam, fentanyl, and S(+)-ketamine; and have a body mass index between 18 kg/m^2^ and 30 kg/m^2^.

### Exclusion Criteria

The exclusion criteria include patients who have increased intracranial or intraocular pressure, severe hypertension, severe psychiatric disease and mental system diseases, severe respiratory diseases, hyperthyroidism, liver or kidney dysfunction, or an allergy to midazolam, fentanyl, or S(+)-ketamine; are unwilling to participate in the study; or misuse alcohol or drugs.

### Intervention

#### Preanesthetic Preparation

An experienced anesthesiologist will participate in the management of the entire perioperative period. Patients will be randomly assigned to the intravenous S(+)-ketamine intervention group or placebo equivalent (0.9% sodium chloride) control group. All patients will be continuously monitored with pulse oximetry, noninvasive blood pressure, and electrocardiogram. General anesthesia induction will be provided after saphenous nerve block is performed with 0.375% ropivacaine (20 ml) by ultrasound guidance.

#### Induction and Maintenance of Anesthesia

All patients will undergo anesthetic induction administered by an experienced anesthesiologist per the protocol using dexamethasone (10 mg), midazolam (0.01-0.05 mg/kg), sufentanil (0.2-0.4 µg/kg), etomidate (0.15-0.3 mg/kg), and atracurium (0.3-0.6 mg/kg). A laryngeal mask airway will be inserted followed by muscle effective relaxation. Patients in both groups will be given ondansetron hydrochloride (8 mg) intravenously during anesthesia induction to prevent postoperative nausea and vomiting.

For patients in the S(+)-ketamine group, anesthesia will be maintained with S(+)-ketamine infusion (0.3 mg/kg/h), sedation will be maintained with propofol infusion (4-12 mg/kg/h), and analgesia will be maintained with remifentanil (0.15-0.3 µg/kg/min). The sufentanil dose at induction and the rate of intraoperative remifentanil and propofol infusions are at the discretion of the anesthesiologist in charge of the patient. The assessment of the depth of anesthesia will be based on clinical evaluation. S(+)-ketamine infusion will be stopped 15 minutes before the end of surgery. Propofol and remifentanil infusion will be stopped at the end of surgery. For the control group, other procedures will be consistent; however, S(+)-ketamine (0.3 mg/kg/h) will be replaced by intravenous sodium chloride (0.9%) infusion (0.3 mg/kg/h).

#### Intraoperative Management

Hypertension will be defined as an intraoperative systolic blood pressure exceeding 20% from the baseline value, and hypotension will be defined as 20% of the baseline value. Norepinephrine should be administered if the patient has hypotension and a heart rate (HR) >90 beats per minute; dopamine should be administered when the patient has hypotension and an HR <50 beats per minute; urapidil hydrochloride should be administered if the patient has hypertension and their HR is normal; and atropine should be administered if the patient has normal blood pressure and a HR <50 beats per minute. The dosages are to be determined by the patient’s sensitivity to drugs to maintain stable circulation.

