#### Secondary Outcome Measures

The secondary outcomes are as follows:

1. The NRS score at rest and during movement at 2 hours after surgery.

2. The NRS score at rest and during movement at 48 hours after surgery.

3. The cumulative consumption of opioids, such as pethidine, sufentanil, and morphine, during the first 48 hours after the operation.

4. The number of patients who required additional analgesics, such as opioids (pethidine, sufentanil, or morphine) or nonsteroid anti-inflammatory drugs (acetaminophen or diclofenac) during the first 48 hours after the operation.

5. The total consumption of opioids (pethidine, sufentanil, and morphine) or nonsteroid anti-inflammatory drugs (acetaminophen and diclofenac) during the first 48 hours after the operation.

6. The incidence of nausea and vomiting and adverse central nervous system events at 2, 24, and 48 hours after the operation.

The use of rescue analgesic drugs (types, administration times, and doses) and any adverse side effects (yes or no) will be recorded.

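### Minor wording error: intraoperative hypotension is defined as a fifth of baseline systolic pressure, where a fall of more than 20% below baseline is evidently meant

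*Protocol article*

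**What the plan says.** One sentence under Intraoperative Management sets both blood pressure limits. The first half reads "Hypertension will be defined as an intraoperative systolic blood pressure exceeding 20% from the baseline value". The second half reads "hypotension will be defined as 20% of the baseline value".

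Two drug rules in the same section use the hypotension limit directly: "Norepinephrine should be administered if the patient has hypotension and a heart rate (HR) >90 beats per minute", and "dopamine should be administered when the patient has hypotension and an HR <50 beats per minute". A third rule, for atropine, applies when blood pressure is normal and the heart rate is below 50, so it relies on the same limits indirectly. Doses are left to the patient's "sensitivity to drugs to maintain stable circulation". No other section restates or corrects the definition.

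**The concern.** The two halves of the sentence use different constructions. Hypertension is expressed as a distance from baseline, hypotension as a fraction of baseline, with no word such as below, fall or decrease. Taken at its word, the second half puts the trigger for a vasopressor at one fifth of the patient's usual systolic pressure.

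This is a decision threshold in the intervention section, not background text, and the patients are 65 or older. Someone who followed it exactly would leave severe hypotension untreated. It is also the only definition of hypotension in the article, so it would be the natural one to use if intraoperative hypotension were reported among the adverse events.

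**Working it through.** There is no calculated figure in the plan to reproduce here; the check sets the two halves of the sentence side by side and converts each to mmHg.

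**Inputs**
- Hypotension as written: 20% of baseline (Intraoperative Management).
- Hypertension: more than 20% from baseline, same sentence.
- Baseline systolic pressure (B): not given in the article. A range of 100 to 180 mmHg is assumed, for illustration only.

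**Formulas**
- Hypotension as written: 0.20 × B
- Hypotension as a fall of 20%: (1 − 0.20) × B = 0.80 × B
- Hypertension as a rise of 20%: (1 + 0.20) × B = 1.20 × B

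| Assumed baseline (mmHg) | As written, 0.20 × B | Evidently meant, 0.80 × B | Hypertension, 1.20 × B |
|---|---|---|---|
| 100 | 20 | 80 | 120 |
| 120 | 24 | 96 | 144 |
| 140 | 28 | 112 | 168 |
| 160 | 32 | 128 | 192 |
| 180 | 36 | 144 | 216 |

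**Reading the results**
1. Across the assumed range the written threshold is 20 to 36 mmHg. No choice of plausible baseline rescues it. At a baseline of 140 mmHg, even a pressure that had halved (0.50 × 140 = 70 mmHg) would not meet the definition.
2. Reading the second half in parallel with the first gives a band symmetric about baseline: at 140 mmHg, 112 to 168, or 140 ± 28. This fits the section's stated purpose of keeping the circulation stable; the literal reading does not.
3. The parallel reading leaves one detail open: whether the limit is more than 20% or 20% or more. The hypertension clause uses the strict form, so the strict form is the better inference, but the sponsor should confirm it.

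**Does anything in the analysis depend on it?**
- The primary outcome is the pain score at 24 hours. The adverse-event item among the secondary outcomes is "The incidence of nausea and vomiting and adverse central nervous system events at 2, 24, and 48 hours after the operation". Hypotension is in neither, and it is not in the assessment schedule (Table 1).
- The sample size rests on a pain-score difference of 1.5, an SD of 3, 80% power, a two-sided 5% level and 10% dropout. Blood pressure does not enter.
- On treatment of the arms, apart from the study infusion, "For the control group, other procedures will be consistent". The wording therefore does not favour either group.

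**The case against.** The strongest reply is that this is a copy-editing slip with one sensible reading. The second clause can be taken as a shortened continuation of the first, with the direction supplied by the word hypotension itself. No clinician would wait for 20 to 36 mmHg, and the protocol puts an expert in charge: "An experienced anesthesiologist will participate in the management of the entire perioperative period". The section also reads as clinical guidance rather than a mechanical algorithm. Doses are left to judgement, and no drug is named for hypotension with a heart rate from 50 to 90, so judgement must already fill gaps.

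Two further points have weight. The article condenses a full protocol that is not shown, so the error may exist only in the published English. And 132 of the planned 144 patients had been enrolled by December 2023, so a correction can guide little remaining treatment.

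All of this stands as an argument about severity. It makes harm unlikely and rules out any inference that care was actually affected. It does not make the sentence correct. The allowance for a condensed article covers what is left out, whereas here a threshold is stated and stated wrongly. If the full protocol has it right, the article still needs correcting.

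**Conclusion.** The point holds, as a minor one. The hypotension threshold is wrong as written by a factor of 0.80 / 0.20 = 4 relative to the evident intent, whatever the baseline. The mmHg figures rest on an assumed baseline of 100 to 180 mmHg and show only that the written value is unworkable; they estimate no effect on patients or results.

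The intended meaning is inferred from the hypertension clause and the purpose of the section, since the article never states it. The symmetric 20% rule itself is not in question. The treatment comparison, the sample size and the efficacy analyses are unaffected.

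**What to change.** Reword the sentence so that both limits use the same construction: hypertension is a systolic pressure more than 20% above baseline, and hypotension is a systolic pressure more than 20% below baseline.

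The sponsor should also check whether the faulty phrase stands in the full protocol, and confirm that the intended rule (including whether the limit is strict) was the one applied in theatre. If intraoperative hypotension is reported as an adverse event, the corrected definition should be used. The Safety section provides for recording all adverse events related to the research, and the Discussion names hypotension as a side effect that low-dose S(+)-ketamine may reduce, so such reporting is plausible.

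The cost is a one-phrase correction and a check of the existing document. It changes nothing in the sample size or the analysis and, if the intended rule was the one followed, nothing in the conduct of the trial.

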### Outcome Measures

#### Primary Outcome Measure

The primary outcome is the numeric rating scale (NRS) score at rest and during movement 24 hours after surgery in the surgical ward. The NRS is widely used to assess pain intensity after surgery. The NRS is evaluated on an 11-point scale (no pain: NRS=0; mild pain: 0<NRS<4; moderate pain: 4≤NRS<7; severe pain: 7≤NRS<10; worst pain imaginable: NRS=10).

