### Statistics

The SD will be described for measurement data that follow a normal distribution, and the median (IQR) will be described for measurement data that do not conform to a normal distribution. The student *t* test will be used to compare continuous and normally distributed variables, and the Mann-Whitney U test will be used to compare nonnormally distributed variables. Counts (percentages) will be described for categorical variables using χ^2^ analysis or Fisher exact tests for compilation.

Both primary and secondary outcomes will be based on an intention to treat analysis. SPSS 22.0 software (IBM) will be used for statistical analysis, and a *P* value of <.05 will be considered to be statistically significant.

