### Sample Size

The minimum clinically important difference (MCID) can be used to guide the noninferiority margin for clinical trials and to determine the sample size in a clinical trial [16,17]. The NRS pain score ranges from 0 (no pain) to 10 (worst pain imaginable). The MCID for the NRS that was used for the calculation of the study sample size was 1.3; however, some studies suggest that an MCID of 1.5 or 2 is appropriate [18-20]. The sample size would have been too small if we choose an MCID of 2. Considering a 10% withdrawal or dropout rate, a sample size of 72 patients per group was calculated, with a power of 80%. The MCID determined 1.5 as statistically significant, with an SD of 3 at the 5% bilateral significance level.

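### Two 24 h pain scores share the primary outcome, but the plan gives one unadjusted .05 threshold and a sample size for a single comparison, so 5% error and 80% power do not both hold as written

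*Protocol article*

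**What the plan says.** Under Outcome Measures, Primary Outcome Measure, the protocol article states: "The primary outcome is the numeric rating scale (NRS) score at rest and during movement 24 hours after surgery in the surgical ward". The Methods part of the Abstract agrees: "The primary outcome measure will be the numeric rating scale score at rest and movement at 24 hours after surgery". Neither place ranks the two scores, combines them, or says whether one or both must show a difference.

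The Statistics section compares the groups one variable at a time. For normally distributed measures, the Student *t* "test will be used to compare continuous and normally distributed variables", with Mann-Whitney U otherwise. A single criterion covers all tests: a *P* "value of <.05 will be considered to be statistically significant".

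The Sample Size section gives one set of inputs: "The MCID determined 1.5 as statistically significant, with an SD of 3 at the 5% bilateral significance level". With 80% power and a 10% dropout allowance, it arrives at 72 per group. It does not say whether the 1.5 and the 3 describe pain at rest or pain during movement.

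**The concern.** Pain at rest and pain during movement are two ratings taken under different conditions. Calling them one outcome in the singular does not make them one variable, and no average or composite is defined. Two tests on two variables need a rule that turns two P values into one conclusion. The two natural rules have different costs:

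- **Either score suffices.** There are two chances of a false positive, each at .05, so the error rate for the primary claim exceeds 5%.
- **Both scores are required.** The error rate is controlled, but the trial must succeed twice, so the power is below that of one test.

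The two scores may disagree. On the text as it stands, a result significant on one score only could be read as a success or as a failure. Choosing the reading after the data are known is what a pre-specified primary outcome is meant to prevent. The Results section reports 132 patients enrolled by December 2023 out of 144 planned, so the time left to settle this is limited.

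**Working it through.** **Inputs from the document.** Difference 1.5, SD 3, two-sided 5%, power 80%, dropout 10%, 72 per group (Sample Size); 1:1 allocation (Objective and Trial Design); P<.05 for every test (Statistics).

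**Assumptions not in the document.** (a) The correlation *r* between the test statistics for the two scores, shown from 0 to 0.9. (b) The difference of 1.5 and SD of 3 apply to each score.

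**Step 1: reproduce the 72.** Normal approximation: n = 2(1.960 + 0.842)² × 3²/1.5² = 2 × 7.85 × 4 = 62.8, so 63 per group, and 63/0.9 = 70. A two-sample *t* test needs 63.8, so 64 per group, and 64/0.9 = 71.1, so 72. The stated figure therefore reproduces as one endpoint tested once at two-sided 5%, with no allowance for a second primary score. (The same section also mentions 1.3 as the difference used. That gives 84 per group, 94 with dropout, and does not match 72. It is a separate matter.)

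**Step 2: either score counts, each at .05.** Family-wise error = P(|Z₁| > 1.96 or |Z₂| > 1.96) under no effect, with (Z₁, Z₂) bivariate normal with correlation *r*. At *r* = 0 this is 1 − 0.95² = 0.0975.

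**Step 3: both scores required, each at .05.** The expected value of each statistic is δ = 1.5/(3√(2/n)). At n = 64, δ = 0.5/√(2/64) = 2.83. At n = 72, δ = 3.00. Joint power = P(Z₁ > 1.96 and Z₂ > 1.96) with both means equal to δ. At n = 64 and *r* = 0 this is 0.807² = 0.652.

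**Step 4: Bonferroni, each at .025.** The critical value is 2.24. The power for one given score at n = 64 is 71% (*t* test). The power for at least one score is 1 − P(neither exceeds 2.24 in absolute value) with both means equal to 2.83.

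| *r* | Either at .05: family-wise error | Both at .05, 64 per group: power | Both at .05, 72 per group: power | .025 each, 64 per group: power for at least one |
|---|---|---|---|---|
| 0 | 9.8% | 65% | 72% | 92% |
| 0.5 | 9.1% | 70% | 76% | 86% |
| 0.7 | 8.4% | 72% | 78% | 83% |
| 0.8 | 7.8% | 74% | 79% | 81% |
| 0.85 | 7.5% | 75% | 80% | 80% |
| 0.9 | 7.0% | 76% | 81% | 78% |

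The either-score error is above 5% in every row. The both-required power at the planned 64 evaluable is below 80% in every row.

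**The case against.** **This may be settled in an analysis plan that is not shown.** A testing order or co-primary rule is often set out there, and a journal article condenses. The Statistics section states a general threshold; it does not say, score by score, that each test carries the trial's claim. That limits what can be inferred about intent, and it would be wrong to assert that the sponsor has no rule. It does not remove the point. Which variable is primary, and which variable the sample size serves, are fixed in this document: two scores, one threshold and a one-endpoint calculation, which do not fit together as written.

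**A reader might infer that no rule could deliver both 5% and 80%.** The document does not support that. With all 72 per group evaluable and *r* of about 0.85 or more, requiring both scores gives 80%. A fixed order keeps 5% overall and 80% for the leading score. Bonferroni keeps 5%, with 81% to 92% power for at least one score for *r* from 0.8 down to 0. What can be said is that the text adopts none of these rules, and that the first depends on essentially no dropout when the plan itself allows for 10%.

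**A reader might also infer that a Bonferroni or Holm rule cuts the trial's power to 71%.** That figure is for one given score at the .025 step. If success means at least one significant score, the relevant range is 78% to 92%. Holm's power for a given score is also higher than Bonferroni's.

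**The two ratings may be highly correlated.** They come from the same patient at the same time point, so this is reasonable. It would put the either-score error nearer 7% to 8% than 9.8%. It shrinks the problem but does not remove it.

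**Conclusion.** The point stands in bounded form. Two separate scores are primary, one unadjusted .05 threshold applies, and the 72 per group is a single-comparison figure not assigned to either score. Counting either score gives a family-wise error of about 7.0% to 9.8%. Requiring both keeps 5% but gives about 65% to 76% power at 64 evaluable per group.

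These sizes rest on the assumed correlation range of 0 to 0.9. The power figures also rest on carrying the one stated difference and SD over to both scores. That the sample size was derived for one comparison, with the score unnamed, depends on neither assumption. The defect is one of specification: it can be cured within 144 patients, and it does not show that the trial is too small.

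**What to change.** Before unblinding, make a dated change to the protocol, the registry entry and any analysis plan:

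1. **Preferred.** Name one 24 h score as the sole primary outcome. The document ranks neither, so the choice is the sponsor's. State in the Sample Size section that the difference of 1.5 and SD of 3 refer to that score. Test the other score at .05 only if the first is significant. This keeps the 5% level, and 80% power for the named score, with 72 per group.
2. **If both stay primary,** state one rule and the power that goes with it:
   - Holm or Bonferroni: 5% is kept, with about 78% to 92% power for at least one score and about 71% for a given score at the Bonferroni step.
   - Both required: 5% is kept without adjustment, with power restated as about 65% to 76% at 64 evaluable per group.

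The cost is a wording change with no additional patients. The downside of the preferred option is that the second score cannot be claimed if the first is not significant.
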